## Abstract

**Background:**

Postoperative ileus (POI) occurs in almost all patients after abdominal laparoscopic surgery, resulting in complications and increasing the length of hospitalization. Electroacupuncture has been used as an alternative therapy for gastrointestinal dysfunction, but its efficacy for POI is inconclusive. The study is designed to determine whether electroacupuncture can accelerate recovery from POI.

**Methods/design:**

This study is a three-arm, randomized controlled trial. A total of 105 patients will be randomized into a group receiving electroacupuncture at Tianshu (ST25), a group receiving electroacupuncture at Zusanli (ST36), or a control group in a 1:1:1 ratio. Patients in the electroacupuncture groups will receive electroacupuncture treatment for 4 days from the first day after surgery. The primary outcome consists of the time to first flatus and the time to first defecation. Secondary outcomes include the time to first tolerance of liquid and semiliquid food; the length of the hospital stay; postoperative pain, nausea, and vomiting; abdominal distension; the time to first get out of bed; and postoperative complications. The outcomes will be assessed by the patients themselves every day during hospitalization. Surgeons, nurses, assessors, and statisticians will be blinded to the group assignments. Patients in the two electroacupuncture groups, but not in the control group, will be blinded to the group assignments. The acupuncturists will not be blinded.

**Discussion:**

The aim of this trial is to provide a nonpharmacological therapy for POI and may provide evidence of the effect of electroacupuncture at ST25 or ST36 on POI.

**Trial registration:**

Chinese Clinical Trial Registry ChiCTR1900027466. Registered on 14 November 2019.

**Supplementary Information:**

The online version contains supplementary material available at 10.1186/s13063-021-05564-3.

## Background

Postoperative ileus (POI) is defined as a transient inhibition of gastrointestinal motility caused by abdominal surgery, especially colorectal cancer surgery [1, 2]. POI occurs in all postoperative patients after abdominal surgical procedures, even if minimally invasive techniques are used, and lasts for 2 to 4 days [3]. POI has a significant impact on postoperative recovery, with symptoms such as abdominal distension, pain, nausea, vomiting, delayed exhaust and defecation, the disappearance of bowel sounds, and intolerance to oral feeding [4]. POI is a self-limited functional gastrointestinal disease but decreases the quality of postoperative life and causes serious complications [5]. In addition, POI can lead to longer hospital stays and higher healthcare costs [6–8].

The Food and Drug Administration (FDA) approved alvimopan to treat POI in 2008. However, the efficacy and economic benefits of this drug remain controversial [9–12]. Some clinical trials have shown the effectiveness of several interventions, including the placement of a nasogastric tube (NGT) [13], minimally invasive surgery [14], and the use of alvimopan [15], coffee [16], and chewing gum [17], for treating POI. However, the consensus is that the evidence supporting these treatments is not strong [18, 19]. Therefore, it is necessary to find other effective therapies.

Electroacupuncture is a nonpharmaceutical intervention that is commonly used to treat various functional gastrointestinal disorders [20, 21]. Systematic reviews have found that electroacupuncture can improve POI after colorectal cancer surgery [22, 23]. Multiple acupoints were used in the randomized controlled trials included in the reviews [24–26]. Using acupoint combinations may increase the infection rate of postoperative patients, who are at a high risk of infection [27–29]. Moreover, the effect of acupoint combinations may be weaker than that of a single acupoint for gastrointestinal dysfunction [30]. Thus, using a single acupoint may be a better choice for POI than acupoint combinations. ST25 (Tianshu) and ST36 (Zusanli) are located on the stomach meridian and are two commonly used acupoints in treating POI [31]. However, the effects of electroacupuncture at ST25 or ST36 on treating POI are unclear.

We assume that electroacupuncture at ST25 or ST36 can promote recovery from POI. Accordingly, we have designed a pilot trial to evaluate the therapeutic potential of electroacupuncture at ST25 (EA A) or ST36 (EA B) compared to a control on POI after laparoscopic surgery for colorectal cancer.

The hypotheses are as follows.

H0: Effect of EA A or EA B = effect of the control group

H1: Effect of EA A or EA B ≠ effect of the control group

## Methods/design

### Study design

This single-center, three-arm, prospective randomized trial will be conducted at the Cancer Hospital of the Chinese Academy of Medical Science. The protocol has been registered on chictr.org.cn (No. ChiCTR1900027466) and reported in full accordance with the SPIRIT guidelines. Figure 1 is a flow diagram of the trial.

**Fig 1 Fig1:**
[figure not shown]
EA A Group: electroacupuncture at ST25 (Tianshu acupoint); EA B Group: electroacupuncture at ST36 (Zusanli acupoint)

### Population, recruitment, and ethics

Patients undergoing laparoscopic colorectal surgery will be informed of the intervention measures, intervention time and other trial procedures through advertisements in the hospital. Patients who meet the criteria for inclusion and exclusion after surgery will be provided with the aforementioned information again. Then, each patient will be asked to sign an informed consent form and recruited if he/she agrees to participate in the trial before randomization. The study investigators will be responsible for recruiting patients and obtaining informed consent. The study protocol has been approved by the Ethics Committee of Beijing University of Chinese Medicine and conforms to the Declaration of Helsinki (No. 2019BZHYLL0207).

#### Inclusion criteria

Age above 18 years;Laparoscopic colorectal surgery has been performed;Abdominal surgery has been performed for the first time;American Society of Anesthesiologists (ASA) grade I–III;Willing to provide written informed consent.

#### Exclusion criteria

Laparoscopy needs to be synchronized with other surgeries;Laparoscopy will be followed by open surgery;Intraoperative and postoperative complications requiring intensive care;Taking a long-term medication that affects bowel function, such as Chinese herbs, vitamins or iron sulfates, within a month before surgery;Has received acupuncture within a month before surgery;Has a pacemaker;History of syncope or epilepsy;Epidural anesthesia during surgery;Participation in other clinical studies within the last 3 months;Has stoma creation.

### Randomization and allocation concealment

Patients will be randomly assigned to the EA A, EA B, and control groups in a 1:1:1 ratio. The randomization sequence will be generated by an independent statistician who will not participate in the study using block randomization in SAS 9.3 software. The treatment allocation code will be placed in an opaque envelope labeled with a sequential number. After informed consent is obtained from an eligible patient, the acupuncturist will receive an opaque envelope and begin electroacupuncture treatment on the two EA groups.

### Masking

Patients in the two EA groups, hospital staff (surgeons and nurses) assessors, and statisticians will be blinded to the group assignments, but the patients in the control group will not be blinded because of the particularity of the treatment. The acupuncturists will not be blinded.

### Intervention

#### Electroacupuncture groups (EA A and EA B)

The acupoints in the two EA groups are Tianshu (ST25) and Zusanli (ST36) (which will be located according to the WHO Standard presented in Table 1) [32]. Patients in the EA groups will receive acupuncture treatment at bilateral single acupoints using disposable stainless steel needles, 0.30 mm × 40 mm (Hwato, Suzhou, China). Only acupuncturists with more than 5 years of experience will be allowed to perform the intervention. Acupuncture stimulation will be performed for at least 10 s to achieve “deqi” (a radiating needle sensation accompanied by soreness and numbness), after which a pair of electrodes from an electric stimulator (HANS-200A acupoint nerve stimulator, Nanjing Jisheng Medical Co, Ltd) will be connected to the needle handles at ST25 or ST36. An electroacupuncture waveform with a 2/100-Hz density alternating wave will be adopted, and the intensity of the electric current will be increased up to a level that the patient can perceive and tolerate. The EA group will be treated for 30 min once a day for a total of 4 days from the first day after surgery. Acupuncture interventions will be recorded by the study investigators after each session to ensure patient compliance. The intervention plan is set for 4 days because the pathological status of POI lasts for 2–4 days [33]. In addition, all patients will receive routine standard postoperative care (RSPC).

**Table 1 Tab1:** Location of ST25 and ST36

Acupoint	Location
**Tianshu (ST25)**	On the upper abdomen, 2 cun lateral to the center of the umbilicus.
**Zusanli (ST36)**	On the anterior aspect of the leg, on the line connecting ST35 and ST41, 3 cun inferior to ST35, locate on the tibialis anterior muscle.

#### Routine standard postoperative care (RSPC)

Multimodal pain management (use of nonopioid analgesics).Patient-controlled anesthesia (PCA).Sips of water after the patient has first flatus.Intake of protein and energy-rich nutritional supplements.Mobilization within 24–48 h: the patient will be instructed to ambulate at least once for any length of time between 24 and 48 h after surgery.

#### Control group

Patients in the control group will receive RSPC without acupuncture. At the end of the trial, if a patient is willing to contact us, we will give free acupuncture treatment.

### Primary outcome

The primary outcome is a composite endpoint consisting of the time to first flatus and the time to first defecation [34], which are defined as the time from the end of the operation to the first exhaust and defecation, respectively, and will be recorded in hours in the case report form by patients under the supervision of an assessor during hospitalization. The minimum clinical significance of the primary outcome is 12 h [27].

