## Discussion

POI is a pathological state that always occurs after colorectal surgery and inflicts a considerable financial burden on patients and society. This trial will evaluate the effects of performing EA at ST25 or ST36 in accelerating the POI recovery time.

Although several trials have been conducted, the consensus [19] is that acupuncture is not a recommended treatment for POI, which may be due to the low reliability of trials. This trial fully meets methodological requirements and achieves full randomization of patients and blinding for patients, hospital staffs, outcome assessors and statisticians.

Actual clinical results show that postoperative patients are more likely to accept acupuncture with fewer acupoints, which can reduce the discomfort caused by acupuncture. Thus, we have chosen ST25 or ST36 as treatment acupoints, which have already been proven to be effective for gastrointestinal dysfunction [35–37]. Our aim is to observe whether EA at a single acupoint can promote recovery from POI.

The pathological state of POI lasts for a maximum of 4 days after surgery [33]. Our intervention will last for 4 days after surgery to ensure that every patient is treated with electroacupuncture during the pathological state. In addition, EA with 2/100-Hz stimulation has been proven to be effective in reducing postoperative incision and visceral pain [38, 39].

A limitation of the trial is that visible acupoints in patients in the two groups receiving acupuncture may break blindness. Another limitation is that as all patients will receive RSPC which is based on a protocol for enhancing recovery after surgery [40], it may lead to a ceiling effect, and the efficacy of electroacupuncture may be negatively affected. However, we hope the trial will provide more reliable evidence than previous studies and clarify the value of electroacupuncture as a treatment for POI.

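### A patient who has already passed flatus can be randomised, and that event counts as a primary outcome the allocated arm cannot have affected; the dilution is small

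*Protocol article*

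**What the plan says.** All references are to the protocol article.

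- **Order of entry.** Population, recruitment, and ethics places screening after the operation: "Patients who meet the criteria for inclusion and exclusion after surgery will be provided with the aforementioned information again". Each patient then consents and is "recruited if he/she agrees to participate in the trial before randomization". The inclusion criteria confirm the order: "Laparoscopic colorectal surgery has been performed".
- **Allocation.** Randomization and allocation concealment states: "After informed consent is obtained from an eligible patient, the acupuncturist will receive an opaque envelope". The text gives no time limit from surgery to this step.
- **Eligibility.** The exclusion list does cover events after the operation, namely "Intraoperative and postoperative complications requiring intensive care". Neither list mentions return of bowel function.
- **Treatment.** Sessions run "once a day for a total of 4 days from the first day after surgery".
- **Outcome clock.** Primary outcome defines both components as "the time from the end of the operation to the first exhaust and defecation".
- **Analysis.** Statistical analysis keeps any patient with at least one session or one day of the daily form. It compares times by the Breslow test and requires both flatus and defecation to differ at 0.025.

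**The concern.** Each element is reasonable alone. Together they leave a gap between the start of the clock and the moment of allocation, and nothing requires a patient to be event-free when that gap closes. Someone who passes flatus in the gap is eligible, is randomised, and contributes an observed primary event that no allocation could have changed.

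Such patients add noise and no signal. The Breslow test weights each event time by the number still at risk, so these earliest events carry the largest weights. Because both components must be significant, any power lost on flatus is lost to the primary claim. The question is how much.

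**Working it through.** **Inputs (Sample size section).** Mean time to first flatus 64.8 h (control) and 48 h (EA), difference 16.8 h, SD 21.6 h; defecation 122 h (control), SD 45 h; two-sided 0.025, 80% power, 10% dropout.

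**Assumed, because the article does not give it.** The hour of randomisation, taken as 18, 24 or 36 h after the operation with treatment following at once; and the shape of the distribution, taken as normal or as lognormal with the same mean and SD.

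**1. The plan's own figure.** n per arm = 2 × (2.241 + 0.842)² × (21.6/16.8)² = 31.4, and 31.4/0.9 = 34.9, so 35 per arm. This reproduces. About 31 to 32 patients per arm are evaluable.

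**2. Share with flatus before randomisation.** Normal: Φ((t − 64.8)/21.6). The control distribution is used because it describes untreated patients.

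| t | Normal | Of 105 | Lognormal | Of 105 |
|---|---|---|---|---|
| 18 h | Φ(−2.17) = 1.5% | 1.6 | under 0.1% | about 0 |
| 24 h | Φ(−1.89) = 2.9% | 3.1 | 0.2% | 0.2 |
| 36 h | Φ(−1.33) = 9.1% | 9.6 | 5.0% | 5.2 |

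Defecation at 24 h: Φ((24 − 122)/45) = Φ(−2.18) = 1.5% (normal), and effectively zero under the lognormal.

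**3. Simple dilution.** If a share f cannot respond, the mean difference becomes 16.8 × (1 − f). With 32 per arm the standard error is 21.6 × √(2/32) = 5.4, and power = Φ(16.8(1 − f)/5.4 − 2.241).

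- f = 0: Φ(3.111 − 2.241) = 80.8%
- f = 0.2%: Φ(3.105 − 2.241) = 80.6%
- f = 3%: Φ(3.018 − 2.241) = 78.1%
- f = 5%: Φ(2.956 − 2.241) = 76.2%
- f = 9%: Φ(2.831 − 2.241) = 72.2%

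**4. Rank-test simulation.** 20,000 replicates, 32 per arm, two-sided 0.025, no censoring (where Breslow and Wilcoxon essentially coincide). In the *proportional* model EA shortens only the time remaining after treatment starts. In the *shift* model EA brings flatus forward by 16.8 h but never to before treatment starts.

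| Start | Distribution, model | All eligible | At-risk only |
|---|---|---|---|
| 18 h | normal, proportional | 90% | 92% |
| 24 h | normal, proportional | 91–92% | 94–95% |
| 24 h | normal, shift | 75.0% | 81.0% |
| 24 h | lognormal, either | – | gain of about 0 to 1 point |
| 36 h | normal, proportional | 94% | 99.6% |
| 36 h | normal, shift | 69.3% | 88% |

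A further check at 24 h gave gains of about 3 to 7 points under normal times and about 0 under lognormal times.

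**5. Not all of the gain is removed dilution.** Under normal times an unrestricted 16.8 h shift has 75.6% power. A 24 h start therefore costs 75.6 − 75.0 = 0.6 points and a 36 h start 75.6 − 69.3 = 6.3 points. The gain from restriction at 24 h is larger, 81.0 − 75.0 = 6.0 points, because dropping the early tail also narrows the spread of the times.

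**The case against.** The strongest reply is that this is a design preference. The end of the operation is a coherent origin, it applies equally to every arm, and an all-comers postoperative population is defensible. The hour of randomisation is not in the text, and the flow and schedule figures are not shown. The percentages come from the lower tail of an assumed distribution: at 24 h the normal gives about 3 patients and the lognormal about 0.2. A first session at 36 h on the first postoperative day needs an operation finished by noon and a session late that evening or around midnight. All of this stands, and it limits the size of the point. It does not remove the gap, since eligibility is stated in the article and has no at-risk condition.

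The reply also says, correctly, that excluding these patients has a price. Someone with early flatus is usually still at risk for first defecation, the other required component, and for food tolerance, distension and length of stay.

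Two stronger readings are not supported:

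- **A contradiction with the Discussion.** A reader might infer one from the aim "to ensure that every patient is treated with electroacupuncture during the pathological state". That sentence justifies the four-day course. The Background describes ileus by several features, including distension, nausea, delayed defecation and intolerance of oral feeding, so first flatus does not end it. With control defecation assumed at 122 h on average, an early-flatus patient would normally still be treated during the ileus.
- **A sample with no room for this loss.** A reader might infer it from the 31 to 32 evaluable patients per arm. The calculations do not bear it out: a 24 h start costs 0.6 points under the shift model, and the proportional model leaves power at 90% or more without any change.

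**Conclusion.** The point holds as a minor design weakness. Entry after surgery, a clock from the end of the operation and the absence of an at-risk criterion together allow primary events that precede allocation. They do not favour an arm or inflate the type I error; they pull the flatus comparison slightly towards no difference.

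If randomisation happens by about 24 h, 0.2% to 2.9% of patients are affected. Simple dilution then costs about 0 to 3 points of power (80.8% to between 80.6% and 78.1%), and enrolling only at-risk patients gains about 0 to 7 points. Larger effects need randomisation near 36 h, which is an extreme case, or recovery faster than the plan assumes. The Discussion itself raises a possible ceiling effect from enhanced-recovery care, and faster recovery would raise the affected share. Defecation is barely touched. These sizes rest on the assumed hour of randomisation, the distribution and the effect model, none of which the article fixes.

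**What to change.** 1. Add an exclusion criterion: *first flatus or first defecation has already occurred before randomisation*.
2. Record the date and time of randomisation on the case report form.
3. Keep the end of the operation as the time origin, so that results stay comparable with the figures behind the sample size.
4. Keep in the intention-to-treat analysis every patient whose event falls between randomisation and the first session. The new criterion acts only before allocation and leaves randomisation intact.

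**Cost.** One criterion and one form field. A few percent or fewer of screened patients become ineligible and are replaced. Their defecation and secondary-outcome data are lost, and the population narrows slightly towards slower recoverers. If the sponsor prefers the broader population, step 2 alone would at least let the report state how many primary events preceded randomisation.

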### Secondary outcomes

Secondary outcomes will include the length of the hospital stay; the time to first tolerance of liquid and semiliquid food; postoperative pain; postoperative use of analgesics; postoperative nausea and vomiting; the time to first walk independently; postoperative distension of the abdomen; and adverse events.

The length of the hospital stay is defined as the time from the end of the operation to discharge. The time to first tolerance of liquid and semiliquid food is defined as the time from the end of the operation to the first tolerance of the aforementioned two kinds of food without gastrointestinal adverse reactions. The time to first walk independently is defined as the time from the end of the operation to the first time the patient can get out of bed and ambulate. Postoperative pain will be evaluated regularly at three fixed times per day using the visual analog scale (VAS, from 0 to 10), and the three scores will be averaged. The higher the score is, the more severe the indication of pain and nausea is. Vomiting, nausea, and abdomen distension will be counted once, daily. The abovementioned outcomes will be recorded by the patient on a daily assessment form (DSF) during hospitalization.

Adverse events include postoperative complications and adverse acupuncture events. Postoperative complications, such as fever, intestinal edema, and intestinal anastomotic fistula, will be recorded and graded according to the Clavien-Dindo classification (Table 2) by the assessors. If patients have serious complications after surgery, the participants will be asked to discontinue the trial, and the doctor will administer appropriate treatment. Adverse acupuncture events include subcutaneous hematoma, continuous acupuncture afterfeeling, and itching at the sites of needle insertion and will be recorded by the assessors.

**Table 2 Tab2:** Clavien-Dindo classification

**Grade 1**	Any deviation from the normal postoperative course without the need for pharmacologic treatment or surgical, endoscopic, and radiologic interventions. Allowed therapeutic regimens are drugs as antiemetics, antipyretics, analgetics, and diuretics, and electrolytes and physiotherapy. This grade also includes wound infections opened at the bedside
**Grade 2**	Requiring pharmacologic treatment with drugs other than such allowed for grade I complications. Blood transfusions and total parenteral nutrition are also included
**Grade 3**	Requiring surgical, endoscopic, or radiologic intervention
**3a**	Intervention not under general anesthesia
**3b**	Intervention under general anesthesia
**Grade 4**	Life-threatening complication (including CNS complications) requiring IC/ICU management^a^
**4a**	Single organ dysfunction (including dialysis)
**4b**	Multiple organ dysfunction
**Grade 5**	Death as a result of complications

*Abbreviations*: *CNS* central nervous system, *IC* intermediate care, *ICU* intensive care unit

^a^Brain hemorrhage, ischemic stroke, or subarachnoidal bleeding but excluding transient ischemic attacks

Handling of biological specimens is not applicable to this trial as none will be collected for any outcomes.

The DSF is shown in Table 3. Figure 2 shows the schedule of enrollment, intervention, and assessment.

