### Data management

All data will be collected in case report forms (CRFs) that have been created by study members and will be entered into electronic record form by two independent researchers to ensure the accuracy of the data from the operation day to the discharge day. The investigators will continue to collect data on patients in the ward who have fallen off treatment for as long as possible until the end of the trial (discharge). The data collectors will be trained to fill out the CRFs to ensure the accuracy of the data. Paper files, including the original CRFs (including the baseline data and DSF data) and consent forms, will be kept for more than 5 years after publication. All final data will only be accessed by the study staff and kept strictly confidential. Readers and reviewers who have questions or want to check the original data can contact the corresponding author. Private patient information, including names, home addresses, and telephone numbers, will be kept confidential at all times.

Moreover, an independent Data and Safety Monitoring Board (DSMB) will be set up to review the trial data every month and determine whether the patient needs to discontinue from this trial in the event of complications and seek medical attention. The members of the DSMB are selected and appointed by the sponsor and include physicians and ethicists who are not involved in the study. The role of the DSMB is to help sponsors maintain a rigorous study design, give appropriate attention to subject protection, review and evaluate clinical efficacy and safety data collected during the study, and evaluate cumulative reports of serious adverse events.

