### Statistical analysis

All statistical analyses will be performed according to the intention-to-treat (ITT) principle, which includes patients who will have received electroacupuncture at least once or who will have completed DSF for at least 1 day.

All paper data will be input into the electronic CRF and analyzed by SPSS 20. Measurement data will be presented as the mean ± standard deviation (M ± SD) or median and quartile spacing, and counting data will be presented as the composition ratio and percentage. Demographic and other baseline data will be compared by ANOVA and the chi-square test. The primary outcome and the time endpoints of the secondary outcomes will be compared by the Kaplan-Meier Breslow (generalized Wilcoxon) test. The incidence of pain, nausea, and abdominal distension; the frequency of vomiting; and the incidence of complications will be analyzed by the chi-square test or Mann-Whitney *U* test. Factors that may affect the results such as the stage and metastasis of colorectal will be recorded in the baseline. If these factors are unbalanced at baseline, we will use these factors as stratification factors to control the potential influence. The statistically significant *P* test level will be less than 0.025 for the primary outcome and less than 0.05 for the secondary outcomes. The primary outcome will be considered to be statistically different when both the first flatus time and the first defecation time are statistically different between the groups. The missing data will be filled using the last observation carry-over method. No additional, subgroup or interim analyses are planned for the trial.

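### Serious complications are met by discontinuing the trial rather than electroacupuncture alone, and this is not reconciled with the plan to follow patients to discharge (minor)

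*Protocol article*

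**What the plan says.** All references are to the protocol article.

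- **Secondary outcomes:** "If patients have serious complications after surgery, the participants will be asked to discontinue the trial". The rule is not restricted to the electroacupuncture (EA) arms.
- **Data management, DSMB paragraph:** the board is to "determine whether the patient needs to discontinue from this trial in the event of complications".
- **Data management, first paragraph:** "The investigators will continue to collect data on patients in the ward who have fallen off treatment for as long as possible", with discharge named as the end point.
- **Outcomes exposed:** "The length of the hospital stay is defined as the time from the end of the operation to discharge". Postoperative complications are an outcome too, graded by Clavien-Dindo, with anastomotic fistula among the examples. Grade 4 in Table 2 is a "Life-threatening complication (including CNS complications) requiring IC/ICU management".
- **Exclusion criteria:** "Intraoperative and postoperative complications requiring intensive care". Eligibility is assessed after surgery and before randomisation, so the discontinuation rule concerns events that arise or worsen after enrolment.
- **Control group:** "Patients in the control group will receive RSPC without acupuncture".
- **Statistical analysis:** analysis is by intention to treat. A patient counts after one EA session or one day of the daily form. For gaps, "The missing data will be filled using the last observation carry-over method".

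**The concern.** Stopping a treatment and leaving a trial are different things. Under intention to treat, a patient who stops EA because of a complication should still contribute outcomes. The two sentences on complications speak of the trial, not of EA, and neither says that follow-up continues.

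The trigger makes this more than loose phrasing. A serious complication is a post-randomisation event, is itself an outcome, and is linked to gut recovery and length of stay. If such patients leave, what is lost is probably among the longest stays, together with any later or escalating complication. Some first-defecation times would also be pending. Carrying a last observation forward cannot restore these: a first defecation or a discharge that has not yet happened has no earlier value to carry.

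**Working it through.** **1. The rules side by side**

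| Question | Complication rule (Secondary outcomes; DSMB paragraph) | Follow-up rule (Data management) |
|---|---|---|
| What ends? | Trial participation, as worded | Treatment |
| Who? | Participants in any arm | Patients off treatment and in the ward |
| Does data collection continue? | Not stated | Yes, to discharge, as far as possible |

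A patient on the ward who stops EA because of a complication fits the follow-up rule well. Two groups fit less clearly:

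- patients moved to intensive or intermediate care, who are no longer on the ward;
- controls, unless routine care counts as the treatment they have stopped.

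**2. The plan's own figure**

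The rule itself carries no number. The Sample size section supplies the inputs used below: flatus 48 h (EA) and 64.8 h (control), SD 21.6; defecation 86 h and 122 h, SD 45; two-sided alpha 0.025, power 80%, dropout 10%, 35 per arm.

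For flatus, n = 2(z₀.₉₈₇₅ + z₀.₈)² × SD²/Δ² = 2 × (2.241 + 0.842)² × (21.6/16.8)² ≈ 31.4, so 32 per arm. Then 32/0.9 = 35.6, so 36, against the stated 35. That is close enough to use these inputs.

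**3. Which primary times would be pending at an early exit?**

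Assume normal times. With a = (t − μ)/SD, P(T > t) = 1 − Φ(a) and E[T | T > t] = μ + SD × φ(a)/P(T > t). The exit times of 72 h and 96 h are illustrative choices.

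| Outcome, exit time | Control pending | EA pending |
|---|---|---|
| Defecation, 72 h | 86.7% | 62.2% |
| Defecation, 96 h | 71.8% | 41.2% |
| Flatus, 72 h | 36.9% | 13.3% |
| Flatus, 96 h | 7.4% | 1.3% |

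These are the chances that a patient who leaves at that hour has the event outstanding. They are not the share of an arm that would leave. Gamma times with the same means and SDs give 88.2% and 56.0% for defecation at 72 h, so the pattern does not depend on normality.

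**4. Effect on the primary outcome if the last observed hour is entered (an assumption)**

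Exit at 72 h with defecation pending:

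- Control: a = (72 − 122)/45 = −1.111; E = 133.2 h; entered 133.2 − 72 = 61.2 h early; arm mean moves 61.2/35 = 1.75 h.
- EA: a = (72 − 86)/45 = −0.311; E = 113.5 h; entered 113.5 − 72 = 41.5 h early; arm mean moves 41.5/35 = 1.19 h.
- One such patient in each arm changes the 36 h difference by 1.75 − 1.19 = 0.56 h, against the 12 h taken as clinically relevant under Primary outcome.

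Any further delay caused by the complication itself is not included.

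**5. Power**

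The complication rate is not given. Suppose 2% to 15% of patients are lost on top of the planned 10% dropout. Evaluable patients per arm are 35 × 0.9 × (1 − s), that is 30.9 at s = 2% and 26.8 at s = 15%. Power goes from 79% to 73% for flatus and from 82% to 75% for defecation. At 5% extra loss it is 78% and 80%.

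**6. Secondary outcomes**

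Any exit before discharge leaves length of stay incomplete. How often this would happen, and how unevenly by arm, cannot be derived from the article.

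**The case against.** The strongest reply is that the plan already covers these patients. Data management has data entered from the operation day to the discharge day and promises continued collection after treatment stops. A patient with a serious complication who stays in hospital is an obvious case for that promise. Neither complication sentence says that collection stops or that recorded data are discarded. The DSMB decides case by case. The triggering complication is still graded, and the patient stays in the analysis set. Detailed withdrawal procedures are also something an article may leave to the full protocol.

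Much of this stands. A reader might infer that the sections flatly contradict each other. They do not: a consistent reading exists, and the fault is that the article does not state it. A reader might also infer that controls must be lost because they have no treatment to stop. That fails if routine care is read as their allocated treatment. Nor do the pending proportions mean that most controls would lose a defecation time, since only patients who leave are affected.

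The 0.6 h figure has limits of its own. It concerns means, whereas the planned comparison is the Kaplan-Meier Breslow test, in which a pending time could be censored at exit. Such censoring would still be informative, but that was not computed. The poor fit of last-observation carry-forward to event times exists however a patient leaves, and adds no weight here.

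What the objection does not remove is that the rule, as stated twice, ends trial participation on an outcome-related event. That is a matter of what the text says, not of missing detail.

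**Conclusion.** The point holds as a minor one. The wording on serious complications is not reconciled with the plan to collect data to discharge. Read literally, it can cause outcome-related loss of length of stay, later or escalating complications and a few pending defecation times, especially for patients moved off the ward.

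The effect on the primary outcome is probably small: about 0.6 h on a 36 h difference for one pending patient per arm. This rests on normal times, an exit at 72 h and entry of the last observed hour. The power loss is modest over the assumed range of extra loss. The main exposure is in the secondary outcomes, and its size is unknown because no complication rate is given. A reader might infer that the primary comparison is materially biased; nothing in the article supports that.

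**What to change.** Reword Secondary outcomes and both paragraphs of Data management along these lines:

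> A serious complication may lead the treating clinician to stop electroacupuncture only. In all three arms, on or off the ward, time to first flatus, time to first defecation, complications and length of stay are recorded until discharge and analysed as randomised, unless consent is withdrawn.

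In the follow-up sentence, refer to all randomised patients instead of only those in the ward and off treatment.

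The cost is protocol wording. The sample size is unchanged, collection to discharge is already planned, and clinical care of the complication is unaffected. The small downside is that the assessor may have to complete entries for a patient who is too ill to do so or has moved to another unit.
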